## Schedule

After informed consent, all participants will be asked to submit data relative to the presence and characteristics of headache and neck and shoulder pain (September 2007), and to keep a diary (web-based) for one month (October 2007, baseline period).

The participants will be randomized (cluster-randomization) in two groups (study and control group) according to departments distribution (September-October 2007).

At month 2 (November 2007) an instruction program will be administered to the study group only. The intervention consists of brief shoulder and neck exercises to be performed several times a day, a relaxation exercise and instructions of how to reduce hyperfunction of the craniofacial and cervical muscles during the day (see: Intervention).

The control group, instead, will not receive any cognitive program.

Both groups will again fill in the diary during month 7 (April 2008).

At beginning of month 8 (May 2008, beginning of the second phase of the study), the same instruction program (Intervention) will be administered to the control group.

Both groups will again fill in the diaries during month 13 (October 2008, end of the study).

The study design according to time flow is reported in Fig.1

[figure not shown]

Fig.1 . Study design

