### **Controls**

In the control group during the first 7 months (phase 1), no Intervention will be performed nor any training instruction provided; the participants will be asked only to keep the diary everyday at months 1 and 7.

At beginning of month 8 (beginning of the second phase), the same Intervention will be administered to the control group, and diaries will be collected again at month 13.

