### **Statistical analysis**

Subjects who will not give informed consent or will not complete the baseline diary (month 1) will be excluded from the analysis. The data will be analysed according to group distribution.

The **principal analysis** will be conducted between intervention and control group for the first phase of the study (months 1-7; Figure 1, line 1).

Analyses will be performed on subjects for which diaries will be completed for months 1 and 7.

The proportion of subjects with more than 50% reduction in headache days (and in neck and shoulder pain days) at the end of the study period will be assessed and compared between the two groups accounting for the cluster-randomized design of the study.

For each subject, the difference (Delta) in the frequency of symptoms between months 7 and the baseline (month 1) will be calculated; the Deltas between the two groups will be compared with parametric and non-parametric tests, where appropriate, taking into account the cluster-randomized design of the study.

Possible baseline differences between the study group and the controls will be evaluated with parametric and non-parametric tests where appropriate; unbalanced factors will be taken into account in the analysis, if necessary.

Explorative subgroup analyses will be performed by age, gender, severity, compliance, diagnosis, and type of job activity.

A **secondary analysis** (Figure 1, line 2) will be conducted within the intervention group, in order to evaluate the persistence of the efficacy of the intervention; the frequency of pain at months 13 will be compared with that observed at months 7.

A further secondary analysis will be conducted in order to compare the efficacy of the program in the intervention group (end of phase 1) and in control group (end of phase 2).

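### Both month 13 secondary analyses mix the programme's effect with calendar time: persistence is October against April, and the phase 1 versus phase 2 comparison has no stated starting diary for the controls

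*Protocol*

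**What the plan says.** The Protocol's Schedule section fixes three diary months. Participants are asked "to keep a diary (web-based) for one month (October 2007, baseline period"). Then "Both groups will again fill in the diary during month 7 (April 2008"), and "Both groups will again fill in the diaries during month 13 (October 2008, end of the study").

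The programme starts at different times in the two arms. "At month 2 (November 2007) an instruction program will be administered to the study group only". At the beginning of month 8 (May 2008), "the same instruction program (Intervention) will be administered to the control group". The Controls section confirms the untreated stretch: "In the control group during the first 7 months (phase 1), no Intervention will be performed nor any training instruction provided".

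The Statistical analysis section then plans two secondary analyses that use month 13:

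- Persistence, within the intervention group: "the frequency of pain at months 13 will be compared with that observed at months 7".
- A cross-phase comparison, to "compare the efficacy of the program in the intervention group (end of phase 1) and in control group (end of phase 2").

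The only change score defined in that section is month 7 minus month 1, and the only period called baseline is October 2007. No starting diary is given for the controls' phase 2 effect. Neither analysis mentions season or calendar time.

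**The concern.** The principal comparison is concurrent: both arms keep diaries in October 2007 and April 2008, so any difference between those months cancels between arms. The two month 13 analyses lack that protection. Persistence is an October-versus-April comparison in one treated arm. The cross-phase comparison sets a phase that ends in April against one that ends in October, and in the second phase both arms are treated.

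If pain days differ between October and April for any reason other than the programme, these analyses can report that the effect faded, kept growing, or was weaker or stronger in the controls, when the programme did the same thing throughout. Persistence at 12 months is a stated secondary objective, so such a result would be read as a finding about the programme.

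**Working it through.** **Inputs from the Protocol.** 2356 subjects, half per group (1178); 444 departments; intracluster correlation 0.15; two-sided alpha 0.05; 50% symptomatic; responders 20% versus 10%; stated power 0.95.

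**The plan's own figure first.** Participants per department: 2356/444 = 5.31. Design effect: 1 + (5.31 - 1) x 0.15 = 1.646. Symptomatic subjects per arm: 589, so the effective number is 589/1.646 = 358. Power for 20% versus 10% is then 0.964 (0.955 with continuity correction), which agrees with 0.95. This design effect is used below. The Protocol gives no figure for the two secondary analyses.

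**Where the swing enters.** Let e be the programme effect, identical in both arms and lasting. Let s be the April level minus the October level without the programme, with the same October level in both years.

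| Analysis | Contrast | Result when the programme is identical |
|---|---|---|
| Principal, month 7 | (e + s) - s | e, no bias |
| Persistence, month 13 minus month 7 | e - (e + s) | -s instead of 0 |
| Phase comparison, controls from April 2008 | (e + s) - (e - s) | 2s instead of 0 |
| Phase comparison, controls from October 2007 | (e + s) - e | s instead of 0 |
| Phase comparison, month 7 level against month 13 level | (e + s) - e | s instead of 0 |
| Month 7 between-arm difference against controls' October-to-October change | e - e | 0 |

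**Size.** Assumptions: SD of change 5 days (range 4-7), all 1178 per arm contributing, and the design effect of 1.646 applying to change scores.

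- Within one arm: SE = 5 x sqrt(1.646/1178) = 0.187.
- Between two arms' changes: SE = 5 x sqrt(2 x 1.646/1178) = 0.264.
- Chance of a false significant result with bias b: Phi(b/SE - 1.96) + Phi(-b/SE - 1.96), where 5% is nominal.

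| Swing | Persistence (b = s) | Phase comparison, once (b = s) | Phase comparison, twice (b = 2s) |
|---|---|---|---|
| 0.25 day | 27% (16-39%) | 16% (10-22%) | 47% (27-66%) |
| 0.5 day | 76% (48-92%) | 47% (27-66%) | 97% (77% to nearly 100%) |

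**Month length alone.** The end-point is days per month; October has 31 days and April 30. At an assumed 4 to 7 pain days per 30 days, the extra day adds 4/30 = 0.13 to 7/30 = 0.23 day to October unless counts are put on a common length.

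**Illustrative simulation.** Assumptions: gamma-distributed personal rates (shape 1, mean 7.2 days), 30-day diaries, pain 10% more frequent in October, and 15% fewer pain days under the programme in both arms.

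- Mean change is -1.7 days (intervention, October to April) against -0.4 (controls, April to October). October-to-October changes are -1.1 in both arms.
- The month 7 between-arm difference is about -1.0 to -1.1, in line with the controls' October-to-October -1.1.
- Responders, with the more-than-4-day threshold taken in October 2007 as the Primary outcome section requires: 17.1% against 12.6%.

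**Responders need separate handling.** A between-arm difference removes untreated response; a within-arm rate keeps it. On the Protocol's own rates, and assuming 20% also respond in phase 2, the first is 20 - 10 = 10 points and the second is 20%. In the simulation with no swing at all, they are about 5.6 points and 13.5%. The contrast that works for mean days therefore creates a false gap for responders.

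**The case against.** A reader might infer that the Protocol sets an October-to-April change against an April-to-October change, so that the swing certainly enters twice. The text does not say so. April 2008 is the natural starting point, being the controls' last diary before the programme, but the only defined baseline is October 2007, and from there the swing enters once. Figure 1, which might settle it, is not shown. That reading also tempts one to re-select symptomatic controls in April, giving 17% against 10% responders. The Primary outcome section ties the threshold to the baseline period, and on that definition the gap narrows to 17.1% against 12.6%.

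It can also be said that the documents give no evidence of a seasonal swing, that calendar confounding is inherent once the controls cross over, that only secondary analyses are affected, and that month 13 falls in the same calendar month as baseline, so an October-to-October analysis is already open to the analyst.

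Most of this stands as a limit on size. It does not remove the point. Persistence is explicitly month 13 against month 7, so it is October against April on any reading. Each plain reading of the phase comparison in the table above contains s or 2s. Leaving the starting diary open also lets it be chosen after the data are seen.

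**Conclusion.** The point holds for both secondary analyses. As written, neither can separate the programme from an October/April difference: the swing enters persistence once, and the phase comparison once or twice depending on a starting diary that the Protocol does not name. The bias is conditional on s, which the documents do not give.

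The error rates rest on the assumed SD of 4-7 days, the design effect of 1.65 and full retention at month 13; fewer completers would lower them. Exact doubling also needs equal October levels in both years.

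It would be wrong to conclude that the collected diaries are of no help: October 2007 is untreated in both arms and season-matched to month 13, and the controls' untreated October-to-April change estimates the swing. It would equally be wrong to extend the criticism to the principal month 7 comparison, which is concurrent and unaffected.

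**What to change.** Amend the Statistical analysis section as follows.

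1. **Persistence.** Keep the month 13 versus month 7 comparison, but add the intervention group's October 2008 versus October 2007 change as the season-matched figure. Report the control arm's untreated October-to-April change beside the month 13 versus month 7 result.
2. **Phase comparison, mean pain days.** Name October 2007 as the controls' starting diary, express counts per 30 days, and compare the month 7 between-arm difference with the controls' October-to-October change. Use this contrast for mean days only.
3. **Phase comparison, responders.** Do not set a between-arm responder difference against a within-arm responder rate. Report the cross-phase responder comparison as descriptive, with the more-than-4-day threshold taken in October 2007.

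The cost is wording only, since all three diaries are already collected from both arms. There are three drawbacks. October-to-October changes are uncontrolled. They assume no year-on-year drift and no regression to the mean. The phase comparison will also have a somewhat wider interval, because its phase 1 term is itself a between-arm difference.
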